## Abstract

**Introduction:**

Chronic musculoskeletal pain often extends beyond pathology alone. Augmented central pain processing is linked to pain severity, persistence and treatment outcomes. A practical clinical tool is needed to identify individuals likely to have persistent or worsening pain, likely due to augmented central pain mechanisms. Quantitative Sensory Testing (QST) offers mechanistic insight, while the Central Aspects of Pain (CAP) Questionnaire captures symptom profiles that potentially reflect central mechanisms. Combining a brief clinical QST protocol with CAP may support early risk stratification and guide personalised pain management.

**Methods and analysis:**

This prospective observational study will recruit 250 individuals with inflammatory arthritis, osteoarthritis, chronic low back pain or fibromyalgia from existing cohorts, primary or secondary care. Participants will complete validated patient-reported outcomes at baseline, 6 and 12 weeks, with no additional intervention. The risk stratification tool completed at baseline will include clinical QST (Pressure Pain Threshold, Temporal Summation of Pain, Conditioned Pain Modulation), tender point count and the CAP questionnaire. Baseline laboratory versions of the clinical QST, plus Heat Pain Threshold, Offset Analgesia and the Central Sensitisation Inventory short form-9 questionnaire, will provide pain profiling to evaluate the predictive validity and psychometric properties of the tool. Data collection will include demographics, medical history, cognitive and neurological assessments and sleep quality via actigraphy (Actigraph wGT3X-BT). Interviews with patients and healthcare professionals will inform refinement, feasibility and acceptability of the tool.

**Ethics and dissemination:**

Ethical approval was obtained from the Yorkshire & The Humber—South Yorkshire Research Ethics Committee (reference number: 24/YH/1062). Findings will be disseminated through peer-reviewed publications, conference presentations and patient-facing summaries and podcasts. The study aims to develop a clinically feasible tool to identify individuals at risk of persistent or worsening pain due to augmented central pain processing, enabling targeted treatment strategies.

**Trial registration number:**

NCT06518278.

STRENGTHS AND LIMITATIONS OF THIS STUDYThe proposed tool integrates mechanistic insight (Quantitative Sensory Testing (QST)) with self-reported symptom profiles to offer a comprehensive assessment of augmented pain processing.The clinical QST protocol mimics the laboratory measures using low-cost equipment already available within the National Health Service in the UK, alongside the short questionnaire, designed to promote implementation.Recruiting individuals with a range of musculoskeletal conditions enhances generalisability across common pain presentations.Maladaptive pain processing is multidimensional where an individual may demonstrate hypersensitivity to one or multiple QST modalities; while core modalities have been included, the full armamentarium could not be performed for practical reasons.

## Introduction

 Pain is a primary symptom of musculoskeletal conditions, affecting 1.7 billion people worldwide.^1^ The International Association for the Study of Pain (IASP) defines pain as an unpleasant sensory and emotional experience associated with or resembling that associated with actual or potential tissue damage.^2^ Chronic pain is categorised based on activation of nociceptors due to actual or threatened damage (nociceptive pain) or lesions or disease affecting the somatosensory nervous system (neuropathic pain),^2^ but these alone often fail to explain chronic musculoskeletal pain.^3^

Musculoskeletal pain manifests as localised, regional or widespread pain.^4^ Peripherally augmented pain is typically localised but may also extend to adjacent regions and be referred. Centrally augmented pain is often widespread, multifocal, fluctuating in location and intensity, and accompanied by comorbidities also found with localised pain: fatigue, sleep and mood disturbances, cognitive impairment and hypersensitivity.^5^

Chronic pain is associated with altered activation, modulation and connectivity of nociceptive pathways in the central nervous system (CNS).^5^ Quantitative Sensory Testing (QST) has demonstrated the presence of localised and spreading pain hypersensitivity in chronic pain conditions.^46^,^12^ Decreased pressure pain threshold (PPT) at the site and away from the site of tissue injury (eg, an arthritic joint) is believed to demonstrate altered CNS processing of afferent nociceptive signals.^9^ Increasing pain during Temporal Summation of Pain (TSP) assessed by repeated painful stimuli^13^ has been attributed to spinal cord facilitation of nociceptive signalling.^14^ Conditioned Pain Modulation (CPM) reflects a proxy measure of efficiency in descending modulatory controls.^15^ Offset analgesia reflects spinal temporal filtering of nociceptive signals.^16^ The CNS mechanisms underlying Offset Analgesia differ from those underlying a CPM effect.^17^ In both cases, the cost, time requirements and reliance on specialised equipment and expertise make it impractical for routine clinical use encompassing these tests. Clinical adaptations of QST, using alternative equipment or approaches, hereafter referred to as Clinical QST, have been developed for neuropathic pain.^18^,^29^ A similar approach could help identify individuals whose pain is likely driven by augmented central pain pathways.

Although QST evaluates augmented central pain processing, it may not fully capture higher-order dysfunction affecting emotion, cognition, sleep and fatigue driven by affective states. Self-report questionnaires may better assess and capture these aspects, with studies showing associations between questionnaire responses and QST outcomes.^30^,^34^ The Central Aspects of Pain (CAP) questionnaire, initially developed for knee pain^35^ and later refined for other musculoskeletal conditions,^36 37^ includes items associated with neuropathic-like pain, fatigue, anxiety, depression, catastrophising, sleep, cognitive impact and pain distribution.^35 38 39^ CAP forms a unitary construct more strongly associated with QST than any individual characteristic alone.^38^ Similarly, the Central Sensitisation Index short form (CSI-9) was developed from medically unexplained symptoms associated with pain not adequately explained by tissue damage.^40^,^44^ While practical, questionnaires lack the mechanistic precision to assess augmented pain pathways indirectly.

We propose integrating clinical QST with questionnaires to develop a risk stratification tool to identify individuals at risk of persistent or worsening pain likely due to augmented central pain processing. This tool is hypothesised to be feasible, reliable and practical for clinical settings, enabling timely and targeted pain management. Its goals are to:

Identify individuals at risk of persistent or worsening pain likely due to augmented central pain processing.Identify those likely to benefit from CNS-targeted interventions.Detect early treatment responses even before symptom improvement.

A targeted approach would move beyond ‘one-size-fits-all’, trial and error approach, reduce unnecessary treatments,^45 46^ improving confidence in medical care, fostering realistic expectations^47^ and potentially healthcare economic benefits. This study co-developed the tool with individuals experiencing chronic musculoskeletal pain, ensuring its relevance, feasibility and impact.

### Objectives

The primary objective is to:

Assess the feasibility, acceptability and reliability of the CAP questionnaire and clinical QST to identify people at risk of persistent and/or worsening pain arising or augmented by augmented central pain processing across a range of musculoskeletal pain conditions.Determine the ability of the clinical QST and CAP questionnaire, alone or combined, to predict persistent and/or worsening pain at 6 and 12 weeks.Determine the ability of clinical QST and CAP alone or combined with other proxy measures of augmented central pain processing, demographics and clinical variables to improve prediction of persistent and/or worsening pain at 12 weeks.Validate clinical QST and CAP in relation to laboratory QST as an outcome measure for augmented central pain processing.Evaluate associations between the risk tool (clinical QST and CAP) and key patient-centred outcomes linked to augmented central pain processing.

The secondary objectives are to:

Determine the ability of the clinical QST and CAP questionnaire, alone or combined, to predict persistent and/or worsening pain at 6 and 12 weeks.Determine the ability of clinical QST and CAP alone or combined with other proxy measures of augmented central pain processing, demographics and clinical variables to improve prediction of persistent and/or worsening pain at 12 weeks.Validate clinical QST and CAP in relation to laboratory QST as an outcome measure for augmented central pain processing.Evaluate associations between the risk tool (clinical QST and CAP) and key patient-centred outcomes linked to augmented central pain processing.

## Methods and analysis

### Study design and setting

This multisite, prospective observational study will recruit adults with inflammatory arthritis, osteoarthritis, fibromyalgia or chronic low back pain. The study design follows the recommendations of the Consolidated Standards of Reporting Trials (CONSORT) 2010 extension for observational studies.^48^ It is reported following the Strengthening and Reporting of Observational Studies in Epidemiology guidelines (online supplemental material 1).^49^ The study started recruitment in October 2024, is currently recruiting and is expected to end in April 2027.

### Patient and public involvement

Patient and public involvement (PPI) follows the National Institute for Health and Care Research UK Standards for Public Involvement framework. Individuals with lived experience of musculoskeletal pain were pivotal in the development of this study. The study was co-designed through online discussions (n=9) and peer reviews with individuals experiencing musculoskeletal pain, influencing decisions on the research theme, assessment measurement tools and the participant journey. The CAP questionnaire was initially developed and later refined with patient and public contributors.^35 36 38 39^

To enhance accessibility and engagement, study materials were co-created, and the participant journey was refined through discussions and walkthroughs of the study visits. Their feedback ensured that materials were clear, relevant and patient-centred.

People with musculoskeletal pain are active members of this paper’s study steering committee and co-authors ([name]). They contribute throughout the study by attending steering group meetings, ensuring lived experience perspectives inform decision-making, supporting study materials and protocol development, refining participant-facing documents and interpreting and disseminating study findings to ensure findings are meaningfully interpreted and communicated from a patient perspective.

[name] were coapplicants on the successful funding applications approved by Arthritis UK and the European Alliance of Associations for Rheumatology (EULAR), who integrated PPI in the review process. This embedded PPI approach ensures that the study remains relevant, feasible and reflective of lived experience, maximising its impact.

### Participants

Inclusion (must meet all criteria):

Aged 18 years or older.One or more of the following physician confirmed or self-reported diagnoses: fibromyalgia, osteoarthritis, chronic low back pain, inflammatory musculoskeletal conditions (eg, rheumatoid arthritis (RA), psoriatic arthritis (PsA), axial spondylarthritis).Musculoskeletal diagnosis and pain onset ≥3 months.Self-reported pain ≥3/10, where 0 is ‘no pain’ and 10 is the ‘worst pain imaginable’ for most days in the 3 months before baseline.

Exclusion (if any of the following apply):

Unable to give informed consent.Terminal or uncontrolled medical or mental health condition precluding them from completing the study protocol or pose a significant risk to themselves or staff.Unable to comprehend spoken to written English, due to not all questionnaires being translated and validated in other languages, and due to the nature of QST, individuals need to fully comprehend the testing procedure to ensure reported outcomes are valid.

Participants will be identified through primary or secondary healthcare services, including Sherwood Forest NHS Foundation Trust, Primary Integrated Community Services, the Investigating Musculoskeletal Health and Wellbeing research cohort^50^ and Central Aspects of Pain in Rheumatoid Arthritis Cohort.^37^ Individuals recruited from primary or secondary care will have a diagnosis done by a physician of one or more of the above conditions. Individuals recruited from the community or research cohorts will have a self-reported diagnosis. Individuals meeting the above criteria will be invited to participate in the study and provided with an invitation pack containing an invitation letter, a participant information sheet, a reply slip and a pre-paid envelope, or a link to access all of these and a form to fill in. Participants will undergo a telephone screening to confirm eligibility, and an appointment will be scheduled at a mutually convenient time. At the study appointment, participants will be screened a final time before providing written informed consent and undertaking study assessments. Recruitment will ensure the study populations represent the four diagnostic groups and display age, sex, social and ethnic diversity representative of the study population. Purposive sampling will be used to ensure that less common conditions, such as inflammatory arthritis, have sufficient power to allow proper analysis. Given the prevalence of multiple long-term musculoskeletal conditions, we anticipate that this approach will yield a representative chronic pain population. All individuals will provide written informed consent prior to participating in the study (see online supplemental material 2). Reasonable travel expenses will be covered. Additional incentives will not be provided.

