### Outcomes

Primary outcomes:

The risk for persistent pain or pain worsening to a clinically important extent, using the risk stratification tool (combined clinical QST and CAP).Sensitivity and specificity of the risk stratification tool to identify people at risk of persistent and/or worsening pain.

Secondary outcomes:

External validity of the risk stratification tool against laboratory QST and validated questionnaires addressing central sensitisation-related characteristics.Internal validity of the risk stratification tool.Pain prognosis: Prediction of pain at 12 weeks by the risk stratification tool, CAP and clinical QST separately.Mechanistic underpinning: Investigate, according to the assessments outlined, which pain mechanisms contribute to risk levels identified using the risk stratification tool.Acceptability and feasibility of the risk stratification tool by patients, healthcare professionals (HCPs) and researchers within both research and clinical environments.Refinement of the risk stratification tool by patients, HCPs and researchers.Inter-rater and intrarater reliability of the risk stratification tool.

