### Data analysis

Pain profiling will be undertaken irrespective of condition. Multivariate modelling (principal component analysis, cluster analysis or latent class analysis) to identify distinct pain patterns.Between-group comparisons (eg, independent T-tests, Mann-Whitney U) will explore between pain profile comparisons.Associations between pain profiles and clinical outcomes (eg, pain intensity, pain-related worrying, disability, quality of life) will be examined.Sensitivity analysis will be conducted between diagnostic groups and between matched samples.We believe that QST will identify somatosensory pain profiles, while CAP will identify psychological hypervigilance pain profiles, each associated with augmented central pain processing. Using the pain profiles combined with pain at 12 weeks, we will identify any relationship between potential augmented central pain processing and pain prognosis at 12 weeks (eg, persistent/worsening pain, pain>patient acceptable symptom state), informed by patterns of pain over 12 weeks and knowledge.Pain prognosis: Bivariable correlations will identify and permit comparison between baseline factors significantly associated with 3-month pain prognosis. Separate multivariable models will determine whether the CAP questionnaire, clinical QST or laboratory QST can increase prognostic precision beyond other clinical and demographic variables significantly associated with pain prognosis. Multivariable modelling will define whether and which combination of the CAP questionnaire and QST importantly improves prognostic determination. The proportion of the prognosis explained by each and by both the CAP questionnaire and clinical or laboratory QST will be determined.The reliability and validity of the stratification tool (combined CAP and clinical QST) will be tested across the study population, with sensitivity analysis conducted across the diagnostic groups, age, sex, social and ethnic strata.Test–retest reliability will be assessed using intraclass correlation between repeated CAP questionnaires and between two raters for simplified clinical QST.RMT, Cronbach’s alpha and confirmatory factor analysis will evaluate internal validity, consistency and factor structure. If multiple constructs with significant residual values exist, this will be further explored using principal component analysis of residuals, the eigenvalue criterion, residual correlations and theoretical understanding.Correlation analysis will assess external validity against self-reported questionnaires and laboratory QST.Mechanistic underpinning: The dataset will be randomly divided into development and validation sets. Exploratory and confirmatory factor analyses will determine whether there are subgroups of the population for whom the stratification tools function differently. Correlations between CAP scores and clinical and laboratory QST indices of augmented central pain processing will be identified. Bivariate and multivariable models will ascertain whether associations may be explained by one or more characteristics linked to maladaptive pain processing (sleep disturbance, fatigue, anxiety, depression, cognitive impact, catastrophising).Relevance to patient-centred outcomes: Bivariate associations between CAP or QST and patient-reported outcome measures scores will be determined through linear regression. The proportion of participant-reported pain or other patient-reported outcome measures explained by CAP scores, clinical and/or laboratory QST measures, will be identified as R^2^ in multivariable regression.Qualitative data will be analysed using reflexive thematic analysis following the stages outlined by Braun and Clarke.^97^ A reflexive journal will be kept throughout the data collection process. Data will be coded inductively primarily, while also being informed by the Normalisation Process Theory^90 91^ commonly used to support evaluation in health interventions and inform the tool’s theoretical acceptability and feasibility. A ‘critical friend’^98^ will code a sample of transcripts independently until consensus is reached. After the consensus is reached, all remaining transcripts will be coded. NVivo V.15 will assist in managing, analysing, and visualising the qualitative data set. A thematic map may also visually represent the main themes developed.

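### The sample is enriched by diagnosis yet called representative; pooled sensitivity and specificity will depend on the recruited mix if tool scores differ by diagnosis, and diagnosis enters the prognostic models only if significant

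*Protocol article*

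**What the plan says.** All references are to the Protocol article.

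- **Participants.** On the mix: "Recruitment will ensure the study populations represent the four diagnostic groups". On how it is reached: "Purposive sampling will be used to ensure that less common conditions, such as inflammatory arthritis, have sufficient power to allow proper analysis". The next sentence, citing how common multiple long-term musculoskeletal conditions are, concludes that "we anticipate that this approach will yield a representative chronic pain population". No number or share per diagnosis is given for the 250 participants.
- **Outcomes.** The second primary outcome is "Sensitivity and specificity of the risk stratification tool to identify people at risk of persistent and/or worsening pain". No diagnostic stratum or target case mix is attached to it.
- **Data analysis.** Reliability and validity of the tool "will be tested across the study population, with sensitivity analysis conducted across the diagnostic groups, age, sex, social and ethnic strata". Also: "Pain profiling will be undertaken irrespective of condition". The pain-prognosis models ask whether CAP or QST adds precision beyond those clinical and demographic variables that prove significantly associated with prognosis. Diagnosis is not named among them.
- **Discussion.** A single tool is expected to serve all conditions, on the premise that they share central processes and pain prognosis. A sensitivity analysis by condition is planned.
- **Content of the tool.** The abstract lists clinical QST, "tender point count and the CAP questionnaire". The Introduction says that CAP covers, among other items, fatigue, sleep, cognitive impact and pain distribution. Experimental procedures classifies fibromyalgia by the Widespread Pain Index and the Symptom Severity Scale.

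**The concern.** Two statements in one paragraph conflict. Raising the share of less common conditions on purpose moves the diagnostic mix away from the one that would arise naturally. Multimorbidity means that participants carry overlapping diagnoses, but it does not restore the natural shares.

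The conflict reaches a primary outcome. Pooled sensitivity is an average of the diagnosis-specific sensitivities, weighted by each diagnosis's share of the events. Pooled specificity is the same average over non-events. If tool scores differ by diagnosis, both averages move with whatever mix was recruited. Some difference is plausible, because the tool's content overlaps with the features used to classify fibromyalgia, but the documents give no scores by diagnosis.

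A second, conditional issue is added value. If 12-week outcome also differs by diagnosis, some of the pooled discrimination may reflect diagnosis alone. The natural safeguard is to have diagnosis in the base model when the tool's increment is judged. The stated rule admits a variable only if it is significant, so this safeguard is left to chance.

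**Working it through.** **The plan's own figure.** 200 / (1 − 0.20) = 250, as in Sample size. This reproduces. No sample size or precision is stated for sensitivity and specificity.

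**Inputs.** The documents give no diagnostic shares, no event rates or tool scores by diagnosis, and no cut-off. These are therefore assumptions:

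- two groups, fibromyalgia (F) and others (O), with F share s of 10%, 25% or 50%;
- normal scores with SD 1, and F higher by 1 SD;
- no predictive value within either group (within-group AUC 0.50);
- cut-off 0.5 SD above the mean of O.

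**Step 1: test-positive rates.** F: 1 − Φ(0.5 − 1) = 0.6915. O: 1 − Φ(0.5) = 0.3085.

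**Step 2: pooled accuracy.** Let a and b be the event rates in F and O.

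- Sensitivity = [s·a·0.6915 + (1−s)·b·0.3085] / [s·a + (1−s)·b].
- Specificity = [s(1−a)·0.3085 + (1−s)(1−b)·0.6915] / [s(1−a) + (1−s)(1−b)].
- AUC = 0.5 + (p1 − p0)·[Φ(1/√2) − 0.5] = 0.5 + (p1 − p0)·0.2602, where p1 and p0 are the F shares among events and non-events.

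Example with a = b = 60% and s = 10%: sensitivity = 0.10 × 0.6915 + 0.90 × 0.3085 = 0.35; specificity = 0.10 × 0.3085 + 0.90 × 0.6915 = 0.65; p1 = p0, so AUC = 0.50.

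Example with a = 80%, b = 40% and s = 25%: p1 = 0.20/0.50 = 0.40; p0 = 0.05/0.50 = 0.10; AUC = 0.5 + 0.30 × 0.2602 = 0.58.

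| Event rates F/O | s | Sensitivity | Specificity | Pooled AUC |
|---|---|---|---|---|
| 60/60% | 10% | 0.35 | 0.65 | 0.50 |
| 60/60% | 50% | 0.50 | 0.50 | 0.50 |
| 70/50% | 10% | 0.36 | 0.67 | 0.52 |
| 70/50% | 25% | 0.43 | 0.63 | 0.54 |
| 70/50% | 50% | 0.53 | 0.55 | 0.55 |
| 80/40% | 10% | 0.38 | 0.68 | 0.54 |
| 80/40% | 25% | 0.46 | 0.65 | 0.58 |
| 80/40% | 50% | 0.56 | 0.60 | 0.61 |

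Sensitivity and specificity move with the mix in every row group, including equal prognosis. AUC rises above 0.50 only when event rates differ. For a tool that does work within diagnosis (AUC 0.638) under equal event rates, pooling lowers the AUC slightly, to 0.609–0.637 over score shifts of 0.5–1.5 SD and shares of 5–50%.

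**Step 3: can diagnosis be left out by chance?** Take 200 completers, 50 with fibromyalgia, event rates 70% and 50%, and a two-sided 5% test.

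- Pooled rate = (50 × 0.70 + 150 × 0.50)/200 = 0.55.
- Null SE = √[0.55 × 0.45 × (1/50 + 1/150)] = 0.0812.
- Alternative SE = √[0.70 × 0.30/50 + 0.50 × 0.50/150] = 0.0766.
- Power = Φ[(0.20 − 1.96 × 0.0812)/0.0766] = Φ(0.53) ≈ 0.70.

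On these assumptions, a real 20-point difference is missed about 30% of the time. At 80% against 40% the same formula gives power above 0.99, so the risk lies in moderate differences.

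**Step 4: precision by group (Wilson 95% intervals, 50% event rate).** A sensitivity of 0.80 in 50 completers (20 of 25 events) has interval 0.61–0.91. In all 200 (80 of 100 events) it is 0.71–0.87.

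**The case against.** **The by-diagnosis question is already addressed in part.** Data analysis plans sensitivity analyses across diagnostic groups and between matched samples, and factor analyses for subgroups in which the tool functions differently. The Discussion repeats the check by condition. A pooled estimate with planned checks by condition is a legitimate design. This stands, and it is why the pooled figure need not be replaced. The checks do not tell the reader to which mix the pooled figure applies.

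**The tool is meant to work across conditions.** Widespread pain, fatigue and sleep disturbance are features that the Introduction attributes to centrally augmented pain, so adjusting them away could remove intended signal. This stands against making a diagnosis-adjusted figure the headline. It does not count against having diagnosis in the base model when added value is claimed.

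**A diagnosis that matters will pass the significance screen.** This holds for large differences only (step 3). The final covariate list may sit in a fuller document, but the article does state the screening rule.

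**Stronger readings that the documents do not support.**

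- A reader might infer that the tool will be credited merely for recognising fibromyalgia. That needs both scores and 12-week outcome to differ by diagnosis. The documents show neither, and the Discussion presumes shared prognosis.
- A reader might infer that diagnostic quotas drive the accuracy. None are set for the 250: the fixed numbers in table 2 are for the interviews. The one condition named for purposive sampling is inflammatory arthritis, not fibromyalgia.
- A reader might take the generalisability statement in the strengths list as a claim of natural prevalence. It refers to the breadth of conditions.

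**Conclusion.** The point holds in a limited form. Purposive enrichment by diagnosis and the expectation of a representative population conflict within one paragraph. The primary sensitivity and specificity, read with the plan to test validity across the study population, describe the recruited mix. On the illustrative assumptions, their dependence on that mix is up to 0.15 on each measure at equal prognosis (fibromyalgia share 10% to 50%). This requires only that scores differ by diagnosis.

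Inflated discrimination is a possibility and no more. For a tool useless within diagnosis and a 1 SD shift, the pooled AUC would be 0.52–0.61 under the unequal event rates tabulated, and 0.50 if prognosis is shared. Overlapping diagnoses, which the plan expects, could shrink these effects, because the calculation uses two separate groups.

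The significance screen is the more practical weakness. It can drop diagnosis from the models that are meant to show added value.

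**What to change.** 1. In Participants, delete or qualify the word representative and describe the sample as diagnosis-enriched.
2. In the pain-prognosis analysis, force diagnosis into the base model whatever its bivariable significance. Use one indicator per diagnosis, since participants may have several.
3. Present sensitivity and specificity by diagnostic group beside the pooled figure, and state that the pooled figure applies to the recruited mix.
4. Where the case mix of the source cohorts and clinics is available, add a supplementary analysis reweighted to a stated target mix.

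**Cost.** No new data are needed, because diagnosis is already collected. The base model spends a few extra degrees of freedom. Estimates by group will be imprecise (about 0.61–0.91 around a sensitivity of 0.80, on the assumptions in step 4) and should be reported as descriptive. Reweighting depends on source case-mix figures that the article does not give, so it can only be supplementary.
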